## Discussion

3

The study protocol presents the starting points and design of a randomized-intervention, multicenter study with the aim of evaluating the effect of the combination duloxetine and PFMT therapy versus duloxetine treatment alone in women with SUI. The study may provide evidence of the efficacy of combined treatment for SUI and indicate an active approach for the treatment of SUI through exercise.

The strength of the study is it promotes an innovative, non-invasive and conservative treatment of strengthening pelvic floor muscles with stabilization exercises in addition to duloxetine treatment. We will use 3 standardized measuring tools: ICIQ-UI SF, OAB-q-short version and I-QoL. Both groups will receive daily oral 80 mg duloxetine (2 × 40 mg), and an innovative PFMT will be added in the experimental group. Interventions will last for 12 weeks, and will consist of exercise 5 times a week for 30 minutes. Education of probands regarding anatomy, physiology, and pelvic floor muscles—so that they properly understand the impact of exercises—will be done by a physiotherapist in collaboration with a nurse 5 times. Subsequently, exercises will be performed at home, and a diary control will be used to ensure compliance.

Based on similar studies, we expect good patient adherence, a low level of patient dropout and agreement with the study protocol. Patients who will be assigned to a duloxetine-only group will be offered the opportunity to exercise after of the 12-week treatment. We expect a 20% subject dropout. The success of our treatment will be a decline of more than 50% in the difficulties associated with SUI symptoms.

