The phase III clinical trial evaluated the clinical efficacy and safety of duloxetine at a daily dose of 80 mg (40 mg twice daily). The clinical trial was double-blinded and placebo-controlled. The clinical file, utilized methods and statistical analysis was similar to those used the phase II clinical trial. The mean percentage change in IEF and mean change in total I-QOL were similarly evaluated. Complete dryness was achieved in 10.5% of duloxetine-treated patients, while only 5.9% of participants in the placebo group achieved dryness. The number of patients who experienced decreased weekly urinary leakage rates (more than half) was significantly higher in the duloxetine group (51%) compared to the placebo group (34%). Nausea was the most common adverse side effect; it occurred in 23% to 28% of the patients taking duloxetine compared to 2% to 7% of participants in placebo group. Although this adverse event occurred in a quarter of all women taking duloxetine, it only caused premature treatment discontinuation in 3% to 6% of cases (it caused premature discontinuation of treatment in 1% of the placebo group). Most women reported nausea when treatment started and throughout the treatment period. Effects only reached a mild or moderate degree (75%–87% of all women with nausea). The nausea was transient in nature and subsided in 40% to 60% of cases after one week and 74% to 86% after 1 month of treatment passed. Thus, after a month of treatment with duloxetine, nausea was only reported in 3% to 7% of all treated women.^[8,11,12]^

Ghoniem et al demonstrated the effect of a 12-week combination of PMFT and duloxetine treatment on women with SUI. The number of IEFs per week, number of pads used, quality of life and subjective evaluation through the PGI-I scale were evaluated. The IEF responder rate in duloxetine vs PFMT group was 56.5% vs 26.1%, median decrease in pads used was 35.3% vs 24.8% and mean increase in I-QoL score was 8.3% vs 7.8%.^[13]^

Maund et al monitored both the benefits and adverse effects associated with duloxetine use for SUI treatment using a meta-analysis. Improvements were reported for reducing SUI symptoms and improving quality of life.^[14]^

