### Primary goal

1.1

The primary goal of this trial is to assess the efficacy of combined duloxetine as comparator and innovative PFMT compared to duloxetine treatment alone in treatment of women with SUI. The primary goal will be monitored based on change in IEFs, according to the International Consultation on Incontinence Questionnaire Short Form (ICIQ-IU SF), over 12 weeks of treatment.

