### Study design

2.1

The Duloxing trial is designed as a randomized controlled intervention and parallel study. The Duloxing study will compare the effect of duloxetine as comparative registered treatment and duloxetine as comparative registered treatment plus innovative PFMT combination therapy within a female population with SUI. Study will examine the effect of authorized registered Duloxetine treatment in the population. The hypothesis states that after 12 weeks of combined treatment, the duloxetine plus PFMT group will have significantly fewer episodes of urine leakage, fewer collection aids and improvements reflected in quality of life assessments compared to the duloxetine alone group. This protocol was approved by the ethics committee of the University Hospital in Martin, Slovakia (number 24012019). All important protocol modifications will be approved by the same ethics committee. Informed consent will be obtain from trial participants by the local clinic of urology. The personal information about potential and enrolled participants will be collected, shared, and protected in concordance with Slovakian low.

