### Recruitment and consent

2.2

The Duloxing study will be performed in 45 community clinics of urology in the Slovakia. The study will use 2 groups in parallel: the experimental group (E) and control group (C). The study will be randomized and controlled in a 1:1 allocation ratio. For the allocation process, sequences will be generated by a computer and designated by a researcher who will not participate further in the study. In this system, the computer generates even and odd patient numbers. Patients with odd numbers will receive duloxetine monotherapy at a daily dose of 2 × 40 mg per tablet for 12 weeks. Patients with even numbers will receive a combined treatment of duloxetine at a daily dose of 2 × 40 mg per tablet for 12 weeks combined with PFMT for the same time period. The generated numbers will be placed in sealed envelopes. Each envelope will contain the group code (E or C). Blinding will prevent intentional selection bias (Table 1).

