### Sample size

2.3

We used power analysis to determine an appropriate sample size; the test strength was set at 0.80 and alpha at 0.05 (type I error). An estimated 63 probands are required for each group (experimental and control). We anticipate a 20% loss in participation and will therefore include a total of at least 158 probands. Based on sample selection, we expect a decrease in incidence after intervention from 10% to 35%. A decrease of more than 50% will be considered a success.

Listed below are the inclusion and exclusion criteria for the DULOXING trial.

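### The >50% decline counted as success has no comparator, measure or unit and is not tied to the between-arm test, so on leakage episodes it could be met with no PFMT effect

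*Protocol article*

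**What the plan says.** Success is stated twice in the protocol article. In 2.3 Sample size: "A decrease of more than 50% will be considered a success". In the Discussion: "The success of our treatment will be a decline of more than 50% in the difficulties associated with SUI symptoms". The first does not say what decreases. The second refers to difficulties linked to SUI symptoms, which is not the name of any outcome in 2.7. Neither mentions the control group.

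The rest of the plan is comparative. The primary goal (1.1) is to assess the combination "compared to duloxetine treatment alone in treatment of women with SUI". The hypothesis (2.1) is that "the duloxetine plus PFMT group will have significantly fewer episodes of urine leakage, fewer collection aids" than the duloxetine-alone group. Data analysis (2.9) compares the two groups before and after the intervention with a GLM and mixed-design ANOVA at P < .05. It names no comparison of the share of women with a given reduction.

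The control arm is on active drug (2.2): "Patients with odd numbers will receive duloxetine monotherapy at a daily dose of 2 × 40 mg per tablet for 12 weeks". The experimental arm takes the same dose.

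**The concern.** The trial asks what PFMT adds to duloxetine. A decline from baseline in women who all take duloxetine mixes the drug effect, the placebo response, regression to the mean and any PFMT effect. Entry requires a questionnaire score of at least 14 and at least seven episodes a week (2.4), so some regression to the mean is likely in both arms, though the article gives no figure for it.

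As written, the article offers two ways to call the result a success: a significant difference between arms, or a decline of more than 50%. Nothing says which governs, and they can disagree in both directions. A large decline in both arms with no difference between them would meet the 50% rule. A real difference between arms with declines under 50% would fail it. In the first case PFMT could be credited with what duloxetine did.

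**Working it through.** **Inputs**
- Planned size (2.3): 63 per group, 20% loss, at least 158 in total. Check: 63 / (1 − 0.20) = 78.75, rounded up to 79 per group; 2 × 79 = 158. The stated total reproduces.
- Share of patients on the same daily dose (80 mg) whose weekly leakage fell by more than half (Introduction, phase III work): "decreased weekly urinary leakage rates (more than half) was significantly higher in the duloxetine group (51%) compared to the placebo group (34" (the last figure being 34%).
- A second cited rate (Introduction, combination study): "The IEF responder rate in duloxetine vs PFMT group was 56.5% vs 26.1" (per cent). The article does not define responder there, so using 56.5% as a >50% reduction is an assumption.
- Scenario: PFMT adds nothing, so the combination arm has the duloxetine-alone rate p.

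**Patient-level reading** (each woman with a >50% fall is a success). Expected successes in the combination arm = n × p:
- p = 0.51: 63 × 0.51 = 32.1, about 32 women.
- p = 0.565: 63 × 0.565 = 35.6, about 36 women.

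The control arm would be expected to have the same number.

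**Arm-level reading** (the arm succeeds if its typical decline exceeds 50%). If 51% of women have a fall above 50%, the median fall is just above 50%. In a sample of 63, the median fall exceeds 50% exactly when at least 32 women have such a fall; for 79, at least 40. The chance is

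P(X ≥ k) = Σ from x = k to n of C(n, x) pˣ (1 − p)ⁿ⁻ˣ

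| True rate p with no PFMT effect | n = 63, k = 32 | n = 79, k = 40 |
|---|---|---|
| 0.34 (cited placebo rate) | 0.004 | 0.002 |
| 0.51 (cited duloxetine rate) | 0.563 | 0.571 |
| 0.565 (second cited rate) | 0.851 | 0.878 |

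The chance of meeting the rule is governed by how well duloxetine alone works. At the placebo rate it is almost nil; at the two cited duloxetine rates it is better than even. The documents give no mean decline, so a reading based on the arm mean cannot be computed.

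**Dependence on the measure.** The ICIQ-UI SF total (2.7.1) runs from 0 to 21 and adds frequency, amount and interference with daily life. A woman entering with seven episodes a week meets a >50% fall at three or fewer (half of 7 is 3.5). A woman entering at 14 points must reach 6 or fewer (half of 14 is 7). Halving episodes does not imply halving the score, so the 51% cannot be carried over without an assumption.

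**The case against.** The strongest reply is that the inference is comparative throughout. The aim, the hypothesis, the planned analysis and the opening of the Discussion all set the combination against duloxetine alone. A reader might infer from the success sentences that the trial would be judged on a before-after change with no comparison. The documents do not support that: the test in 2.9 compares the groups. This part of the objection stands.

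Second, the Discussion speaks of success of the treatment, not of the trial, and a >50% reduction can be read as a responder threshold for individual patients. Such a threshold properly has no comparator of its own, and the Introduction uses one of this kind when citing 51% against 34%. This reading is open, but the text does not state it, and no analysis compares the resulting proportions.

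Third, a reader might infer that about half the women in each arm will meet the rule on the trial's primary score. The 51% is a weekly-leakage figure. It fits 1.1, which puts the primary goal in terms of episode frequency, but the instrument named there is the ICIQ-UI SF, and the article gives no rate for a >50% fall in that score.

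Fourth, a reader might take the 50% bar to contradict the 10% to 35% that 2.3 expects. That phrase may be a range of decreases or a pair of proportions, so no firm contradiction follows. It appears only in 2.3, not in the Discussion.

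**Conclusion.** The point holds in a limited form. The article states a success criterion twice, without comparator, measure or unit, and does not connect it to its own between-arm test. Taken as written and applied to leakage episodes, it can be met with no PFMT effect. About 51% of combination patients would count as successes, and the chance that more than half of 63 would do so is 56% (85% if 56.5% is the right rate). This assumes that the cited duloxetine rates carry over to this population and, for 56.5%, that responder meant a reduction of more than half. For the ICIQ-UI SF score the size is unknown.

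It is not a finding that the trial lacks a comparison or that its main test is invalid. Nor is it a finding about power for a responder endpoint, since the protocol plans none. The absence of a link between criterion and test does not depend on any of the rates.

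**What to change.** Reword the two sentences, in 2.3 and in the Discussion:
- State that the efficacy conclusion rests on the between-arm difference in the primary outcome, tested as in 2.9 at P < .05 and reported with a confidence interval.
- Recast a reduction of more than 50% from baseline as a patient-level responder definition on one named measure. Compare the proportion of responders between arms as a secondary result, as a risk difference with 95% CI.

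The cost is a change of wording and one extra secondary analysis. The authors also give something up: a large decline in the combination arm would no longer be enough to claim success.
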